### Randomisation

Randomisation (1:1 basis) will take place after completion of the baseline testing. Participants will be randomly allocated to one of the following groups: (1) control group or (2) Seniors Exercise Park program group. Randomisation will be stratified by dementia severity (moderate or mild) based on the Standardised Mini-Mental State Examination (moderate sMMSE > 10 but < 20; mild sMMSE ≥ 20 but ≤ 24) [22]. Block randomisation will be undertaken using opaque envelopes, so that blocks of 6–8 participants (3–4 for intervention group and 3–4 for control group) will be randomised at a time. It is expected that recruitment will be undertaken over a period of 6–10 months to achieve a target sample size of 12 participants in each group. Assessors and participants will not be blinded to their respective group allocation. While there are clear benefits from a research perspective to blind assessors, having the same staff undertake assessments and interventions may reduce confusion and improve relationships for the person with dementia where a minimum number of research staff are involved.

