### Statistical methods

#### Sample size estimation and justification

This is a feasibility study with the aim of designing, delivering and evaluating a sustainable physical activity program for people living with dementia in residential aged-care. Leith Park residential aged-care facility has approximately 80 residents, with 37 residents living with dementia (diagnosed as mild to severe dementia by a geriatrician). For the pilot study, we aim to recruit 12 participants for each group. We anticipate 3–4 exercise groups, with a total of 24 participants overall (20 participants completing the study allowing for ~ 15% drop out rate). Our previous trial had 11% drop out from the exercise intervention group [17]. The targeted sample is feasible to be recruited and then followed up for 6 months to allow completion of the trial. The targeted number is also sufficient to provide preliminary results about the feasibility and safety of the exercise program to then optimise it for people living with dementia.

It should be noted that the study is not powered for significant changes in the secondary measures, but that the data from this study will inform sample size calculation for a future large multi-site cluster randomised trial.

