### Statistical analysis

Data for the feasibility and safety components of the study will be analysed as follows (mean, standard deviation and proportion): proportion of participants approached to participate who did commence the program, percentage of participants who complete the intervention, overall percentage of sessions attended, number of participants who dropout, any falls that occur during the exercise sessions, any muscle/joint pain during or after the exercise sessions, and serious adverse events requiring medical attention. Modifications of the exercise program will be reported and a recommended refined structure will be presented at the end of the program.

An acceptable level for feasibility of the program will be based on the following: ≥ 70% adherence of the prescribed number of exercise sessions [24] at the 12-week structured exercise program completion, and a ≥ 60% adherence for the overall 6-month exercise program, with retention of 85% of the sample (estimate 15% drop out).

To determine statistical trends of effectiveness, analyses of the selected outcomes such as cognitive, physical function, quality of life and social measures will be performed to assess the changes within and between groups over time (pre/post). Repeated measures ANOVA with factors of intervention (Seniors Exercise Park program, control) and time (pre-post intervention and follow-up) will be used. A post hoc analysis will be undertaken using the group differences and variability within groups on the secondary measures to determine the required sample size for a future adequately powered study using these outcomes.

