It is important to acknowledge that this is a pilot study and the results might be limited to provide emerging evidence around the suitability of the program for people living in dementia in aged-care. However, the outcomes will generate new evidence around the design of a suitable physical environment and associated exercise program to improve quality of care and quality of life for people living with dementia in residential care in Australia. If successful, the intervention represents a safe, accessible, affordable and highly translatable program, and results could inform future design of the built environment for residential aged-care facilities. In addition, the secondary outcome measures to be assessed in the study will provide preliminary results around the potential effect of the Seniors Exercise Park program on physical and cognitive function to inform a future fully powered study design to assess effectiveness. The Seniors Exercise Park is also scalable as it is available in many countries in the world including the USA and Canada, enabling wide reach to be replicated in other aged-care settings around the world. The real-world setting of this study will enable practical information and knowledge to be generated to enable potential implementation of the program and equipment in existing care facilities worldwide.

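### Effectiveness trends are tied to within-group as well as between-group change with no ranking, so change shared by both arms could be read as programme benefit

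*Protocol article*

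**What the plan says.** The Statistical analysis section of the protocol article opens its plan for the secondary outcomes with a purpose: "To determine statistical trends of effectiveness". The means come in the same sentence: analyses of selected cognitive, physical, quality-of-life and social measures "will be performed to assess the changes within and between groups over time (pre/post"). Within-group and between-group change stand side by side, with no order of priority.

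The model follows: "Repeated measures ANOVA with factors of intervention (Seniors Exercise Park program, control) and time (pre-post intervention and follow-up) will be used". The text does not say which term of this model answers the effectiveness question.

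The last step concerns planning of a later trial: "A post hoc analysis will be undertaken using the group differences and variability within groups on the secondary measures" to obtain the sample size. That is a between-group use of the data.

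The Discussion adds that the secondary measures "will provide preliminary results around the potential effect of the Seniors Exercise Park program on physical and cognitive function". The sample size section states that the study is not powered for these measures.

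**The concern.** Effectiveness in a randomised trial means exercise compared with control. A within-group test asks whether one arm moved from its own baseline. It cannot tell a programme effect from movement that would have occurred anyway, and removing such movement is the purpose of the control arm. The time main effect of the ANOVA, which pools both arms, has the same limitation.

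Shared change is plausible here. The same tests are repeated at baseline, 3 and 6 months, so familiarity may lift scores in both arms. The Control group section leaves control participants free to receive other physical activity and physiotherapy. Dementia is progressive, so the shared change may also be downward. In that case an unchanged exercise arm, read alone, would hide a benefit that the between-group comparison could show.

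At stake is what the pilot says about potential effect. With about 10 completers per arm, the between-group result will be imprecise. A within-group p-value could then become the one that is highlighted, and setting a significant arm against a non-significant one is not a test of their difference.

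**Working it through.** **Inputs from the protocol article**
- Allocation 1:1 (Randomisation section).
- Sample size: "we aim to recruit 12 participants for each group", 24 in all; about 15% dropout; 20 completers (sample size section).
- Same test battery at baseline, 3 and 6 months (Procedure section).

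**The plan's own figure.** 24 × (1 − 0.15) = 20.4, which agrees with the stated 20 completers, or about 10 per arm. The article gives no alpha, power or effect size for the secondary measures, so there is no power figure to reproduce.

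**Assumptions not in the document.** Two-sided alpha 0.05; normally distributed changes; pre-post correlation ρ = 0.7; no treatment effect; the same mean shift in both arms, taken as 0.2, 0.3 or 0.5 SD of the outcome.

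**Step 1: standardise the shift.** The SD of change is √(2(1 − ρ)) = √0.6 = 0.775 outcome SDs. The shift in units of the change SD is d = 0.2/0.775 = 0.258, 0.3/0.775 = 0.387 and 0.5/0.775 = 0.645.

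**Step 2: within-arm test.** With n = 10, the paired t statistic has 9 degrees of freedom and noncentrality d√10 = 0.816, 1.225 and 2.041. The rejection probability is p = P(|T| > 2.262).

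**Step 3: exercise arm significant, control arm not.** The arms are independent with the same p, so this probability is p(1 − p).

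**Step 4: between-arm test.** For two time points, the two-sample t-test on change equals the group-by-time test. The shared shift cancels, so the rate is alpha.

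| Shared shift | p, exercise arm rejects | p(1 − p), exercise arm only | Between-group test |
|---|---|---|---|
| 0.2 SD | 0.113 | 0.113 × 0.887 = 0.10 | 0.05 |
| 0.3 SD | 0.195 | 0.195 × 0.805 = 0.16 | 0.05 |
| 0.5 SD | 0.446 | 0.446 × 0.554 = 0.25 | 0.05 |

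Simulation of 20,000 trials per setting gave 0.113, 0.193 and 0.446 for the exercise arm and 0.050 to 0.051 between arms.

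**Sensitivity.** At a shift of 0.3 SD, correlations from 0.6 to 0.8 give 16% to 27% for the exercise arm. With 12 per arm and ρ = 0.7, the figure at 0.3 SD is 23%. With no shift, the within-arm test keeps its 5%; the excess comes entirely from shared change.

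**Time main effect.** With 10 per arm and a shared shift of 0.25 or 0.5 SD of the change score (a different scale from the table), the pooled time test rejects in 19% and 56% of trials. The between-group test stays at 5%.

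**The case against.** The strongest reply is that the plan already contains the right analysis. It is one two-factor model, not a set of separate paired tests, and its group-by-time term is exactly the contrast wanted. The reference to change within and between groups may only describe the model's within-subject and between-subject factors. Naming the decisive term is detail that an article may leave to a fuller document. The outcomes are secondary, the article says they are unpowered, and the Discussion leaves effectiveness to a later trial.

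Much of this stands. The model does supply the correct contrast, and the stakes are limited. It does not remove the point, because the article does more than stay silent: it names within-group change as a means of judging effectiveness, level with between-group change.

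A reader might infer more than the document supports, in four ways:
- That shared change *would* be reported as benefit. No section says that an arm-specific p-value will be read this way; it could be.
- That the future trial would rest on a within-arm result. The planned calculation uses group differences, with within-group variability supplying the SD.
- That the misleading pattern occurs in 20%, 31% or 50% of trials. Those rates count every trial with exactly one significant arm, including those where it is the control arm; the pattern that would flatter the programme is half of that.
- That unblinded assessment is a source of the shared drift. It can affect the arms differently, and a between-group contrast would not remove it.

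**Conclusion.** The point holds as a limited one. The effectiveness sentence admits within-group change as evidence without ranking it below the between-group comparison, and within-group change cannot separate a programme effect from change common to both arms. Under the stated assumptions, the exercise-arm test rejects two to nine times as often as the between-group test (0.113/0.05 = 2.3; 0.446/0.05 = 8.9).

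The size rests on the assumed shared shift and on the correlation, neither of which the article gives. The mechanism does not depend on their values, but the sign of the shift matters: an upward shift could suggest a benefit that is not there, and a downward one could mask a benefit in a within-arm reading. The acceptability criteria for feasibility, which are adherence and retention, are untouched.

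**What to change.** Amend the effectiveness sentence in the Statistical analysis section to say that any trend of effectiveness rests only on the between-group difference in change, that is, the group-by-time contrast, at 3 months and at 6 months, each with a 95% CI. Add that within-group changes are reported as means and SDs without p-values and that neither they nor the time main effect are evidence of effectiveness.

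This takes one or two sentences and needs no new data or participants. It also brings the sentence into line with the planned sample size calculation, which already uses group differences. The cost is that fewer nominally significant results will be available to report.

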### Study population

#### Inclusion criteria

Older people from the Leith Park aged-care facility will be recruited if they meet the following inclusion criteria: (1) aged 60 years or older and reside at the aged-care facility; (2) have been diagnosed with mild to moderate dementia, OR suspected to have dementia by the aged-care staff and a screening test score of Standardised Mini-Mental State Examination (sMMSE > 10), OR have cognitive problems that, in the opinion of the experienced staff, puts them in the cognitively impaired domain with suspected mild to moderate dementia, and a screening test score of sMMSE > 10 [22]; (3) are able to stand by themselves with or/without hand support; (4) are able to walk without manual (physical) assistance from staff and; (5) are able to follow simple exercise instructions.

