#### Physical function measures

Physiological measures of strength, balance and functional mobility will be assessed using the following validated tests:(i)Functional lower limb muscle strength using the five times sit to stand test [25]. Participants will be asked to sit on a chair (43 cm high) and stand up (with arms crossed over their chest) five times. The time taken to complete the sit to stand will be measured (seconds).(ii)Exercise tolerance and functional mobility using the two-minute walk test [26]. Participants will walk in a marked area for 2 min at their comfortable pace. The distance covered during the 2 min will be recorded. The length of walkway will be around 10–15 m, based on available length of the facility corridor.(iii)Dynamic balance using the step test [27]. Participants will be asked to place one foot onto a 7.5cm-high step and then back down to the floor repeatedly as fast as possible for 15 s. The number of steps completed in the 15s period for each leg will be recorded. The step test is a test of dynamic standing balance, only takes approximately 1 min to administer, has been shown to have good retest reliability (ICC = .868) in people living with dementia [28], and demonstrated significant improvement in another Seniors Exercise park study (ENJOY translation study) in older people without cognitive impairment [19].(iv)Walking speed using the 4 meters walk test [29]. Participants will be asked to walk 4 m at their usual walking pace. Gait speed will be defined by distance (in meters) divided by time (in seconds). Participants will start walking 2 m before the 4m walkway, and finish walking 2 m after the 4m walkway.

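### The two-factor repeated-measures ANOVA for the secondary outcomes makes poor use of incomplete follow-up, baseline values and the severity stratum; an adjusted mixed model on all follow-up visits would serve better

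*Protocol article*

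**What the plan says.** The Statistical analysis section names one method for the cognitive, physical, quality-of-life and social outcomes: "Repeated measures ANOVA with factors of intervention (Seniors Exercise Park program, control) and time (pre-post intervention and follow-up) will be used". It introduces this with "To determine statistical trends of effectiveness, analyses of the selected outcomes" and refers to change both within and between groups. It does not say which ANOVA term is the comparison of interest, and it mentions no covariate and no handling of missed visits. The same section then uses the group differences and within-group variability to calculate the sample size of a later, powered study.

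Three other statements bear on this:
- Randomisation: "Randomisation will be stratified by dementia severity (moderate or mild) based on the Standardised Mini-Mental State Examination".
- Randomisation: "Randomisation (1:1 basis) will take place after completion of the baseline testing". The baseline value is therefore unaffected by allocation.
- Sample size estimation and justification: "we aim to recruit 12 participants for each group", with 20 of the 24 expected to complete at roughly 15% dropout. It adds that the secondary measures are not powered.

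**The concern.** The named model suits this design poorly in three ways.

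**Missed visits.** Classical repeated-measures ANOVA needs a complete row of baseline, 3 and 6 months. A resident who leaves after month 3 contributes nothing, although a 3-month value exists. The Feasibility section itself expects low mood, anxiety and declining mobility to hinder participation, so dropout related to outcome is plausible.

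**Baseline.** The pre-treatment value is a level of the time factor, not a covariate. The group-by-time term is then a comparison of change scores, while the group main effect averages in a visit made before randomisation.

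**Stratum.** Severity restricted the randomisation but is absent from the analysis.

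What is at stake is the quality of the effect and SD estimates passed to the next trial. The feasibility, safety and supervision outcomes are not touched.

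**Working it through.** **1. The plan's own figures.** Inputs from the sample size section: 12 per group, hence 24; about 15% dropout; 20 completers. 24 × (1 − 0.15) = 20.4, and 20 / 0.85 = 23.5, which rounds up to 24. The figures reproduce.

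**2. Loss under complete-case ANOVA.** 24 − 20 = 4, and 4 / 24 = 17%. If instead each follow-up visit were missed independently with probability m (an assumption), complete cases are 24 × (1 − m)²: 21.7, 19.4 and 17.3 for m = 5%, 10% and 15%.

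**3. What each term estimates.** Take an effect δ that is constant at 3 and 6 months and zero at baseline. The group main effect targets (0 + δ + δ) / 3 = 2δ/3. The group-by-time term compares changes from baseline and is not diluted in this way.

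**4. Precision of covariate adjustment against change.** With equal variances and correlation r between baseline and follow-up, the change score has variance proportional to 2(1 − r) and the baseline-adjusted outcome to 1 − r². The ratio of adjusted to change is (1 + r) / 2. The protocol gives no r, so a range is shown. Estimating the covariate slope costs a factor of 1 + 1/(20 − 4) = 1.0625 with 20 completers.

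| r (assumed) | (1 + r)/2 | Variance cut | Change ÷ adjusted | Same, after dividing by 1.0625 |
|---|---|---|---|---|
| 0.5 | 0.75 | 25% | 1.33 | 1.26 |
| 0.7 | 0.85 | 15% | 1.18 | 1.11 |
| 0.9 | 0.95 | 5% | 1.05 | 0.99 |

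**5. Simulation, random dropout.** Assumptions: 12 per arm, true effect 0.5 SD, about 15% lost before month 6, equal correlation between visits. The SE of the complete-case change contrast was compared with that of an analysis using all visits and adjusting for baseline and stratum: 0.449 against 0.394 at r = 0.5 (12% lower), 0.348 against 0.327 at 0.7 (6% lower), and 0.199 against 0.197 at 0.9 (1% lower). Adding the stratum to a complete-case analysis already adjusted for baseline gave no gain: 0.397 without it and 0.401 with it at r = 0.5.

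**6. Simulation, dropout in the exercise arm related to the 3-month change.** Correlation decayed with time (0.6 to 0.9 between adjacent visits), and every leaver had a 3-month value. Against a true 0.50, the complete-case change contrast averaged 0.57 to 0.72. Complete-case covariate adjustment averaged 0.56 to 0.65. The all-visits adjusted analysis, in which missing 6-month values were predicted from baseline, month 3 and group as a stand-in for the mixed model, averaged 0.49 to 0.50. When dropout was unrelated to change, the complete-case change contrast showed no bias.

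**7. Consequence for the next trial.** Required size goes as 1/effect². Holding the SD fixed, planning on 0.57 or 0.72 when the truth is 0.50 gives (0.50/0.57)² = 0.77 or (0.50/0.72)² = 0.48 of the size needed.

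**The case against.** The best defence is that this is an unpowered pilot whose acceptability rule rests only on adherence and retention, and that about 10 completers per arm will give imprecise estimates under any model. That stands. In step 6 the bias of 0.07 to 0.22 SD is smaller than the standard error of the same contrast, about 0.28 to 0.51. It limits how serious the point is, but it does not make the named model the better one.

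Several stronger readings are tempting, and the documents do not support them:
- *Residents with a missed visit will be discarded.* The protocol does not say so. The loss follows from the classical form of the method, and a fuller document may handle missing visits.
- *The estimates are biased.* Only if dropout is related to outcome.
- *Baseline is ignored.* It is a level of time, so the group-by-time term already compares changes. What is absent is baseline as a covariate.
- *The effect is diluted by one third.* Only if the group main effect is the test. The stated aim of assessing change over time points to group-by-time, although the term is not named.
- *Omitting the stratum costs precision.* Severity is a between-person factor and cancels from a change contrast unless it affects change. The simulation showed no gain. The argument for including it is consistency with the randomisation.
- *A large precision gain is certain.* The only reliability figure in the protocol is the step test's retest ICC of .868. This is not a 3-month correlation and is probably an upper guide. At that value (1 + 0.868)/2 = 0.934, a cut of about 7%. After the small-sample factor the ratio is 1.071/1.0625 = 1.01, almost nothing.
- *The frailest residents lose their sit-to-stand result.* Eligibility covers those who "are able to stand by themselves with or/without hand support", while the test asks them to "stand up (with arms crossed over their chest) five times". This is a separate question of outcome definition: the article gives neither the scoring of residents who cannot do it nor their number.
- *Uncontrolled multiple testing or an underpowered efficacy claim.* The protocol disclaims power and states no alpha or significance rule, so no error rate can be attached to it.

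**Conclusion.** The point holds as an improvement to a stated method. The two-factor ANOVA, in its usual complete-case form, would lose about 4 of 24 residents, including usable 3-month data. It also uses baseline less efficiently than covariate adjustment and does not reflect the stratified randomisation. The precision gain from the whole change is modest: about 12%, 6% and 1% off the SE at assumed correlations of 0.5, 0.7 and 0.9. Protection against outcome-related dropout is the stronger reason. It depends on leavers having a 3-month value and on dropout being explained by observed data; baseline adjustment of complete cases alone does not provide it. The primary outcomes and the target of 24 are unaffected. The change is worth making because these estimates are to size the next trial.

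**What to change.** Replace the ANOVA sentence with wording to this effect: each listed secondary outcome will be analysed, with residents in the group to which they were randomised, by a linear mixed model on all available 3- and 6-month values. Fixed effects will be baseline value, sMMSE stratum, group, visit and group-by-visit. The adjusted between-group difference at 3 and at 6 months will be reported with its 95% confidence interval. Within-group changes may be described but will not be treated as evidence of effect.

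The model does not retain everyone: a resident with neither follow-up visit contributes no outcome data. The number of such residents should be reported by group.

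Cost: a change of analysis wording, one or two degrees of freedom in a small sample, and slightly more analysis work. No extra residents, visits or measurements are needed.

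### The future trial's sample size is to be determined from group differences observed in about 10 completers per arm, which is too imprecise to serve as the effect-size input

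*Protocol article*

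**What the plan says.** The last sentence of the Statistical analysis section of the protocol article gives the rule for sizing a later, fully powered study: "post hoc analysis will be undertaken using the group differences and variability within groups on the secondary measures to determine the required sample size". Two inputs are named: the observed group differences and the within-group variability.

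The section on sample size estimation and justification gives the scale and the purpose:
- The target is stated as "we aim to recruit 12 participants for each group", "with a total of 24 participants overall (20 participants completing the study" after allowing for dropout.
- It acknowledges that "the study is not powered for significant changes in the secondary measures".
- It adds that "the data from this study will inform sample size calculation for a future large multi-site cluster randomised trial".

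The Design and setting section names a single aged-care facility. Under Randomisation the unit is the individual: "Participants will be randomly allocated to one of the following groups". The Discussion repeats that the secondary outcomes are meant to inform a fully powered study.

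**The concern.** Informing the next trial is a stated purpose of this pilot, and the article fixes a rule for doing so. The protocol concedes that it cannot detect effects on the secondary measures, yet it makes the observed effects on those measures an input to the next sample size. Required sample size varies with the inverse square of the assumed effect. Sampling error in the effect is therefore magnified in the result: a chance overestimate gives a trial that is too small, and a chance underestimate gives one that is very large. A zero or reversed difference gives no usable figure.

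There is a subsidiary issue. The future trial is described as cluster randomised, but the two listed inputs contain no clustering term. Applied as written, the rule returns the size of an individually randomised trial.

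**Working it through.** **Inputs from the protocol article.** 12 per arm, 24 in total, about 20 completing with roughly 15% dropout (sample size section); 1:1 individual allocation (Randomisation); one facility (Design and setting). No target difference, SD, alpha, power or ICC is given for the secondary measures. The values used for these below are assumptions.

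**The plan's own figure.** 24 × 0.85 = 20.4, and 20 / 0.85 = 23.5, which rounds up to 24. The 24-to-20 arithmetic is sound and is not in dispute.

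**Precision of the observed difference.** With n per arm, the SE of a standardised difference is approximately √(2/n).
- n = 10: √0.2 = 0.447. The 95% half-width is 1.96 × 0.447 = 0.88 (normal), or 0.94 using t on 18 df.
- n = 12, if nobody dropped out: √(2/12) = 0.408, half-width 0.80. Full retention would change little.

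**Effect on the derived sample size.** Assume two-sided alpha 0.05 and 80% power, so that n per arm = 2 × (1.96 + 0.8416)² / d² = 15.70 / d². For each assumed true effect, 200,000 pilots of 10 per arm were simulated and the observed d was put into this formula.

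| Assumed true d | n per arm needed | Pilots with zero or negative difference | Of the rest, resulting trial under 80% power | Under 80%, as share of all pilots | Of the rest, under 50% power |
|---|---|---|---|---|---|
| 0.3 | 175 | 25% | 67% | 0.67 × 0.75 = 50% | 52% |
| 0.5 | 63 | 13% | 58% | 0.58 × 0.87 = 50% | 37% |
| 0.8 | 25 | 4% | 52% | 0.52 × 0.96 = 50% | 26% |

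The 50% column is near-constant because any roughly unbiased estimate exceeds the truth about half the time. The imprecision shows in how far wrong the answer is. At d = 0.5 the central 95% of observed effects runs from −0.39 to 1.52. The quartiles of the derived n per arm, over all pilots, are 24 and 395 against 63 needed, and 33% of pilots give less than half of what is needed.

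**Precision of the SD.** For a pooled SD on 18 df, the 95% limits are 0.76 to 1.48 times the estimate, so n varies by a factor of 0.57 to 2.19. The SD is a proper pilot output but needs an allowance. The upper 80% one-sided limit multiplies the variance, and hence n, by 18 / χ²(0.20; 18) = 1.40, which is √1.40 = 1.18 on the SD.

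**Clustering.** Between-facility variance cannot be estimated from one facility. The three to four exercise groups could at most show class-level clustering within the intervention arm. The design effect is 1 + (m − 1) × ICC. Over an assumed ICC of 0.01 to 0.20 it is 1.11 to 3.2 with 12 residents per facility and 1.23 to 5.6 with 24. Applied to 63 per arm (d = 0.5), this gives 70 to 202 and 78 to 353 per arm.

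**The case against.** **The consequence lies outside this trial.** The primary outcomes are feasibility, safety and supervision needs, with their own stated criteria. The protocol calls the secondary results preliminary, and the next trial will have its own protocol and review. This stands, and it limits the weight of the point. It does not remove it, because the article states the rule and says that it will *determine* the size.

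**Within-group variability is a legitimate pilot output.** Agreed. The objection here is to the other named input.

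**The percentages are illustrative.** They depend on the assumed effect and on a post-only comparison, whereas the plan is a repeated-measures analysis with a baseline. This also stands. Using the baseline in both pilot and future trial acts like a larger standardised effect, which is why a range up to 0.8 is shown. Even there, about half of all pilots lead to an underpowered trial.

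Three stronger readings are tempting but not supported:
- A reader might infer that the plan claims to estimate an ICC from this pilot. It does not. The sample size section says only that the data will inform the cluster trial, and an external ICC could be added later. The clustering matter therefore belongs in the remedy.
- A reader might infer that the outcome with the most favourable difference will be chosen for sizing. No such selection rule is stated.
- A reader might infer that a pre-stated target guarantees adequate power at the true effect. It does not. With a true effect of 0.4, a target of 0.5 and the upper 80% SD limit, 67% of trials would still be under 80% power at 0.4. The case for a minimum important difference is that it fixes what is worth detecting and does not depend on chance in 20 people.

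**Conclusion.** The point holds for the effect-size input. Ten completers per arm give a 95% half-width of about 0.9 SD, which cannot separate a negligible effect from a large one, so the observed difference should not set the next trial's size. Under assumed true effects of 0.3 to 0.8, 25% to 4% of pilots would give no usable figure, and about half of all pilots would give a trial with under 80% power. The half-width follows from the protocol's own numbers. The percentages rest on the assumed effects, two-sided alpha 0.05, 80% power and a simple two-group comparison.

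The clustering matter is secondary: the listed inputs contain no clustering term and one facility cannot supply a between-facility ICC. Nothing here affects the conduct of the pilot or its feasibility and safety conclusions.

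**What to change.** Replace the last sentence of the Statistical analysis section with wording to this effect: the future trial will be sized on a pre-stated minimum important difference for one named outcome. This pilot will supply the SD of that outcome (taken at an upper confidence limit, for example 80% one-sided), the baseline-to-follow-up correlation and retention. The observed group difference will not be used as the effect size. Because the future trial is to be cluster randomised across sites, the design effect will use an ICC from external multi-facility sources over a stated range.

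The group differences can still be reported descriptively with confidence intervals. The cost is one sentence of wording and no new data. The downside is that the future sample size may be larger than a favourable pilot estimate would have suggested.
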